## Abstract

**Background:**

Technological support using e-health mobile applications (m-health) is a promising strategy to improve the adherence to healthy lifestyles in breast cancer survivors (excess in energy intake or low physical activity are determinants of the risk of recurrence, second cancers and cancer mortality). Moreover, cancer rehabilitation programs supervised by health professionals are needed due to the inherent characteristics of these breast cancer patients. Our main objective is to compare the clinical efficacy of a m-health lifestyle intervention system alone versus an integral strategy to improve Quality of Life in breast cancer survivors.

**Methods:**

This therapeutic superiority study will use a two-arm, assessor blinded parallel RCT design. Women will be eligible if: they are diagnosed of stage I, II or III-A breast cancer; are between 25 and 75 years old; have a Body Mass Index > 25 kg/m^2^; they have basic ability to use mobile apps; they had completed adjuvant therapy except for hormone therapy; and they have some functional shoulder limitations. Participants will be randomized to one of the following groups: integral group will use a mobile application (BENECA APP) and will receive a face-to-face rehabilitation (8-weeks); m-health group will use the BENECA app for 2-months and will received usual care information. Study endpoints will be assessed after 8 weeks and 6 months. The primary outcome will be Quality of Life measured by The European Organization for Research and Treatment of Cancer Quality of Life Questionnaire Core and breast module. The secondary outcomes: body composition; upper-body functionality (handgrip, Disability of the Arm, Shoulder and Hand questionnaire, goniometry); cognitive function (Wechsler Adult Intelligence Scale, Trail Making Test); anxiety and depression (Hospital Anxiety and Depression Scale); physical fitness (Short version of the Minnesota Leisure Time Physical Activity Questionnaire, Self-Efficacy Scale for Physical Activity); accelerometry and lymphedema.

**Discussion:**

This study has been designed to seek to address the new needs for support and treatment of breast cancer survivors, reflecting the emerging need to merge new low cost treatment options with much-needed involvement of health professionals in this type of patients.

**Trial registration:**

ClinicalTrials.gov Identifier: NCT02817724 (date of registration: 22/06/2016).

## Background

Cancer is one of the most incident diseases worldwide. Over 14 million new cancer cases occur every year, but are projected to reach approximately 22 million by 2030 [1]. Among all cancer types, breast cancer is the most commonly diagnosed cancer in women, and approximately 4.4 million women worldwide live with a diagnosis of breast cancer [2]. Fortunately, the survival rate is very encouraging; the estimated number of deaths from breast cancer is estimated to be less than one-third of new cases [1]. Developments in screening and improved treatments for breast cancer have led to improved survival, and it is beginning to be regarded as a chronic disease [3, 4]. This new perspective of the disease has led to a growing need for long-term treatments [4] with an integrative strategy that takes into account the patients’ lifestyles and physical, cognitive and emotional impairments [5–7].

Regarding the importance of the patients’ lifestyles (in physical activity and diet), the literature highlights the importance of maintaining healthy lifestyles to reduce the risk of recurrence, secondary cancers or death. There is strong evidence about the efficacy and safety of exercise and healthy diet to improve the patients’ quality of life (QoL) [8, 9] and reduce the effects of cancer [10, 11]. Recent research reveals that even when patients know the benefits of interventions aimed at promoting energy balance among cancer survivors (in terms of intake and physical activity), it is unrealistic to expect that most of them, who have a strong sedentary habit, will comply with the current good practice guidelines [10, 12]. In addition, survivors report difficulties in adhering to and maintaining an appropriate lifestyle [12]. Consequently, this energy imbalance increases the risk of cancer recurrence [13] and, along with the functional limitations and emotional/occupational imbalance, reduces the QoL of breast cancer survivors (BCS) [14]. New strategies with a comprehensive approach of support must be developed to improve the adherence and motivation of these patients and to reduce the high cost involved in creating individualized exercise programs and diets [15]. Currently, technological support is a promising strategy that could improve issues, such as barriers of distance, time, cost and motivational aspects [16]. Telehealth systems, which are based on computers and mobile applications (m-health), offer a promising approach for both dietary and physical activity assessments [17] and the patients’ motivation can be significantly increased through the immediate feedback provided by these systems [18]. A recent study has developed a mobile application to simultaneously collect data on diet and physical activity in adults [17], but, to our knowledge, no programs exist that simultaneously collect data on diet and physical activity in cancer patients and provide immediate feedback with individualized recommendations.

In addition to the need to improve these patients’ lifestyles, the patients may experience physical, cognitive and emotional impairments. The most common upper body symptoms reported by BCS are related to shoulder impairments [19–21], although much research has supported the practice of performing early exercises to avoid limitations of range of motion (ROM) in the shoulder [22, 23]. Moreover, cognitive impairment occurs in 10%–50% of these women [24, 25], and the emotional distress caused by shifts in social support and the fear of recurrence and death has also impacted women’s wellbeing [26, 27]. The performance of daily tasks (such as activities in daily living, work, and leisure tasks) are influence by all these complications and, along with unhealthy lifestyle habits, affect the overall QoL [22].

In this sense, occupational therapy is an effective intervention to improve the patients’ QoL, ROM or distress in different conditions [28–30]. However, to our knowledge, the only published randomized controlled trial evaluating occupational therapy in BCS is an intervention aimed at reducing the limitations of rural patients in their daily activities [31]. The authors found that a telephone-based problem-solving occupational therapy intervention program was feasible and had positive effects on the patients’ function, QoL and emotional state. However, the study had methodological limitations, such as a small simple size and intervention bias. Other previous studies with the aim of evaluating the effects of occupational therapy on cancer patients had several limitations, such as including any type of cancer [32–36], the use of a non-randomized controlled trial (RCT) approach [33–35, 37, 38], and pilot studies [31, 36] involving very few patients [31, 33, 36–38].

This study arises from the need to establish an integrative and multidisciplinary strategy to support BCS by taking advantage of the features of these two proposals: first, the functionality and independence provided by a mobile application that patients can use when and wherever they choose; secondly, the imperative need for a supervised face-to-face intervention by a health professional, due to the inherent characteristics of these patients. Our study aims to compare the clinical efficacy of an m-health lifestyle intervention system alone versus an integrative strategy that also includes a face-to-face intervention in BCS. In this manuscript, we describe the design and methods of the study.

## Methods

### Objectives

The main objective of this RCT is to assess if an integrated strategy that uses an m-health system in addition to a face-to-face treatment is better than the use of the m-health system alone to improve the immediate and long-term QoL of BCS. Second, we want to examine the effects of the interventions on the overall impact on functionality, body composition, anxiety and depression, physical measurement, lymphedema and cognitive function. The integral group will use the m-health and receive three occupational therapy sessions each week for an 8-week period. We will also study the effect of a 24-week period without rehabilitation on the studied variables. We hypothesize that support care based on an Occupational Therapy-supervised rehabilitation program will promote functionality and the combination with the mobile system will improve the patients’ lifestyles and QoL, reduce distress, and improve cognitive function and arm mobility.

### Research design and methods

The present study is a parallel group, assessor-blind, superiority RCT that will be conducted using assessments at baseline and immediately after the 8-weeks intervention. Follow-up measurements will be collected for 24 weeks after the end of the 8-week intervention period, resulting in a total trial data collection period of 32 weeks. We will use two separate assessment days to avoid fatigue in patients. In Table 1 is shown the study assessment schedule.

**Table 1 Tab1:** Study assessment schedule

Assessment	Baseline	Post-intervention (8 weeks)	Follow – up (24 weeks)
Informed Consent	x		
Day 1 testing			
Sociodemographic data	x		
Anthropometric data, pressure/rate heart	x	x	x
Accelerometry (1 week)	x	x	x
Body Composition (DEXA)	x	x	x
Minnesota	x	x	x
Self-efficacy Physical Activity questionnaire	x	x	x
EORTC QLQ-C30	x	x	x
EORT QLQ-BR23	x	x	x
Day 2 testing			
WAIS-IV^a^(subtest)	x	x	x
Trail Making Test (TMT)	x	x	x
Handgrip strength	x	x	x
Lymphedema	x	x	x
Hospital Anxiety and Depression Scale	x	x	x
DASH	x	x	x
Goniometry	x	x	x

^a^Working memory and processing speed subtest

### Participants

A total of 80 eligible (see inclusion criteria below) BCS will be randomized into the integral group (*N* = 40) or the m-health group (*N* = 40). For feasibility, the study is conducted in three waves. During the first year of the study (from January to December 2016), we will prepare protocols, establish the measurement techniques, and enrol the first 25 women in the study. At the beginning of the second year of the study (between January and April 2017), we will enrol an additional 30 women, and in the third stage, we will enrol the remaining 25 women. In summary, the target sample size of 80 BCS will be achieved in these 3 waves.

The integral group will receive the m-health plus an 8-week occupational therapy onsite program, and the m-health group will only use the app. Participants will be enrolled in this study by oncologists from the Hospital Virgen de las Nieves (Breast Unit) and the Hospital Clínico San Cecilio, Granada (Spain). The Research Ethics Committee of the province of Granada approved this study.

### Eligibility criteria

Eligible women require: 1) to be between 25.0 and 74.9 years-old, 2) to be diagnosed of stage I, II or IIIA breast cancer, 3) to have medical clearance of participation, 4) to be overweight or obese, according to the *Spanish Society for the Study of Obesity* (SEEDO) [39], 5) to have basic ability to use mobile apps or living with someone who has this ability, 6) completion of adjuvant therapy except for hormone therapy, 7) to have some functional or ROM limitations measures by goniometry and the Disabilities of the Arm, Shoulder and Hand (DASH) questionnaire, and 8) to have signed informed consent and have interest in improving lifestyle.

The exclusion criteria were defined as follows: history of cancer recurrence, to have had chronic disease or orthopaedic issues that would interfere with ability to participate in this rehabilitation program, or to have had uncontrolled hypertension (diastolic pressure > 95 mm Hg).

### Outcome measures

The primary outcome measure is QoL. The secondary outcome variables include body composition, active range of motion (AROM), functionality, anxiety and depression, and cognitive function. Other variables of interest include muscular strength and free-living physical activity.

### Primary outcome measure

Quality of life: *The European Organization for Research and Treatment of Cancer Quality of Life Questionnaire Core 30* (EORTC QLQ-C30) version 3.0 [40]: We will use the EORT QLQ-C30 to assess QoL. This questionnaire is one of the most widely used instruments to measure QoL in cancer patients. The QLQ-C30 is composed of both multi-item scales and single-item measures, as well as five functional scales, three symptom scales, a global health status/QoL scale, and six single items. The scores must be averaged and linearly transformed to obtain a range of scores from 0 to 100, with a higher score representing a greater response level. Thus, a high score for a functional scale represents a healthy level of functioning and a high score for the global health status represents a high QoL, but a high score for the symptom scale represents a high level of symptomatology [41]. The test/retest reliability is high for all scales, ranging from 0.82 to 0.91 [40].

*The European Organization for Research and Treatment of Cancer Breast Cancer-Specific Quality of Life Questionnaire* (EORT QLQ-BR23) [42]: This questionnaire is a breast cancer module of the EORTC QLQ-C30 that contains 23 items rated on a four-point scale ranging from 1 (not at all) to 4 (very much). The items assess the side effects of therapy, arm symptoms, breast symptoms, body image, and sexual function. Additionally, there are single items assessing sexual enjoyment, anxiety caused by hair loss, and future outlook. The scores range between 0–100 points. The procedure for scoring the breast cancer module is the same as the EORTC QLQ-C30 [41]. For scales evaluating function, a higher score represents a higher level of functioning. For scales evaluating symptoms, a higher score indicates more severe symptoms. The reliability has been shown to be high to moderate (Cronbach’s α ranged between 0.46 – 0.94) [42].

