### Sample size

The sample size and power calculations for this trial were obtained through overall Health-Related QoL (HRQoL) using EORTC QLQ-C30 version 3.0 [40], and taking into account previously reported data [67] a minimally important difference from 5 to 10 points was considered. Assuming that integral group increase HRQoL in BCS in compared with m-health group [18] we can detect differences of at least 5% with a power of 90% and an α of 0.05 with two groups (Integral group and m-health group) of 36 participants assuming similar standard deviation (approximately 7 points). A maximum loss at follow-up of 10% will be allowed to face a possible drop-out rate [9]. Hence, we will recruit 80 BCS (40 in each group). Fig. 1 shows the flow diagram of the study participants.

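### The primary outcome is two whole questionnaires (23 scores) with no lead score, while the trial is sized on one score at a single undivided alpha

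*Protocol article*

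**What the plan says.** - **Abstract, Methods.** Quality of life is the primary outcome, measured by the EORTC "Quality of Life Questionnaire Core and breast module". Both instruments are named and no scale is singled out.
- **Outcome measures.** "The primary outcome measure is QoL", with no score or visit attached.
- **Primary outcome measure.** Both questionnaires are described under this heading. The QLQ-C30 has "five functional scales, three symptom scales, a global health status/QoL scale, and six single items". For the BR23, "The items assess the side effects of therapy, arm symptoms, breast symptoms, body image, and sexual function", and then: "Additionally, there are single items assessing sexual enjoyment, anxiety caused by hair loss, and future outlook". No total across scales is defined for either instrument.
- **Objectives.** The question is whether the integrated strategy "is better than the use of the m-health system alone to improve the immediate and long-term QoL of BCS". Neither horizon is ranked first.
- **Sample size.** The calculations "were obtained through overall Health-Related QoL (HRQoL) using EORTC QLQ-C30 version 3.0". A single alpha of 0.05 is used, no visit is given, and the BR23 plays no part.
- **Data analysis.** The main analysis is a repeated measures ANCOVA. The section does not say which score it applies to or which model term decides.

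**The concern.** A sample size calculation is a statement about one hypothesis test. Here that test concerns one QLQ-C30 score, but the outcome labelled primary is a set of 23 scores from two instruments. The two statements do not describe the same trial.

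At stake is what a positive or negative result would mean. As the primary outcome is worded, a difference on any one of the 23 scores could be presented as a primary finding, and no pattern of results is defined as failure. This matters in a superiority trial whose Discussion says a positive result would bear on whether health systems include occupational therapy in survivorship care.

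**Working it through.** **1. The plan's own figure.** Inputs from the Sample size section: difference 5 (written as a percentage, taken here as points on the 0–100 scale), SD 7, alpha 0.05, power 0.90, 36 per group, 10% loss. Sidedness is not stated.

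n per group = 2 × SD² × (z_alpha + z_power)² / difference²

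- One-sided: 2 × 49 × (1.645 + 1.282)² / 25 = 33.6, so 34 (35 with the t distribution). This is within 2 of the stated 36.
- Two-sided: 2 × 49 × (1.960 + 1.282)² / 25 = 41.2, so 42 (43 with the t distribution). Power at 36 per group is 0.86.
- Loss: 36 / 0.90 = 40 per group, 80 in total, as stated.

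On either reading this is the size for one comparison at an undivided alpha. The sidedness is a separate matter and is not pursued here.

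**2. Count of scores under the primary heading.**

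- QLQ-C30: 5 + 3 + 1 + 6 = 15
- BR23: 5 areas + 3 single items = 8
- Total: 15 + 8 = 23

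**3. What 23 unadjusted tests would do.** Assume each score is tested once at two-sided 0.05 and there is no true effect.

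- Under independence, the chance of at least one false positive in either direction is 1 − 0.95^23 = 0.693.
- Counting only false results that favour the integral group, it is 1 − 0.975^23 = 0.441.

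The scores are correlated, and the article gives no correlations. The table assumes normal test statistics with one common correlation, with all scales oriented so that higher is better.

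| Assumed correlation | Either direction | Favouring integral group |
|---|---|---|
| 0 | 69% | 44% |
| 0.3 | 58% | 30% |
| 0.5 | 45% | 23% |
| 0.7 | 31% | 15% |

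The nominal values are 5% and 2.5%.

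**4. Two visits.** Testing the 8-week and long-term visits separately would give 23 × 2 = 46 comparisons, and 1 − 0.95^46 = 0.906 under independence. This is an upper count, because a repeated measures model can cover both visits in one term.

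**5. Could the present sample size carry all 23 scores?** Use Bonferroni over 23 scores, two-sided, with the same difference of 5 and SD of 7 assumed for each.

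- Alpha = 0.05 / 23 = 0.00217, z = 3.065.
- n = 2 × 49 × (3.065 + 1.282)² / 25 = 74.1, so 75 per group; 75 / 0.90 = 83.3, so 84 after loss.
- Power at 36 per group: the standardised difference is 5 / (7 × √(2/36)) = 3.030, and Φ(3.030 − 3.065) = 0.49.

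A multiplicity rule added later would thus control the error rate but leave about 49% power for any given score, against the planned 90%.

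**The case against.** The strongest reply is that the lead score can already be inferred. The Sample size section uses overall HRQoL on the QLQ-C30. The Primary outcome measure section says a high global health status score means high quality of life, and the Outcome measures section calls the primary outcome quality of life. Read together, these point to the global health status/QoL scale, and the rest could be description of the instruments. This stands in part: it identifies the probable intention. It does not remove the conflict, because the Sample size section never calls that score primary and the Abstract still includes the breast module.

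A reader might go further the other way and infer that all 23 scores at both visits, 46 tests, are co-primary at 0.05, and that any one of them is enough. The article does not say so. It gives no success rule, sets alpha once for one quantity, and plans a model that need not test the visits separately. Nor can one conclude that the trial has no control of the false-positive rate: a statistical analysis plan that is not shown may hold a testing hierarchy, and its absence from a condensed article is not a fault.

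Two further features might be cited as making this worse: functional and symptom scales run in opposite directions, and BR23 reliability goes down to 0.46. The article explains the scoring direction. Low reliability costs power on a scale but does not raise the false-positive rate. Neither belongs to this point.

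**Conclusion.** The point holds as a conflict within the article. Two whole questionnaires are declared primary in the Abstract and the Methods, while the sizing covers one QLQ-C30 score at one undivided alpha. This concerns the choice of primary endpoint, which the article itself states, and not a detail left to an analysis plan.

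The size is conditional. If the 23 scores were each tested at two-sided 0.05, the false-positive chance would lie between 31% and 69% in either direction, or between 15% and 44% in favour of the integral group, for correlations from 0.7 down to 0. Those correlations are assumptions. Separate tests at the two visits would raise the figures, with 46 comparisons as the ceiling. Over this range every value is at least six times its nominal level (31% against 5%; 15% against 2.5%), so the conclusion does not depend on the exact correlation.

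**What to change.** Amend the Abstract and the Outcome measures, Primary outcome measure and Data analysis sections so that they agree with the Sample size section:

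- Declare the QLQ-C30 global health status/QoL score, which best matches the score used for sizing, as the sole primary endpoint.
- Name one deciding contrast from the repeated measures model at one assessment. The 8-week visit, with the long-term visit tested next in fixed sequence, is one reasonable choice. The documents do not dictate it, and the sponsor should choose the visit before outcome data are seen.
- Move the other QLQ-C30 scales and all BR23 scales to secondary, reported with confidence intervals.

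The cost is wording in the protocol and, where it carries the same outcome, the registry entry. Alpha stays at 0.05 and the change adds no patients to the planned 80. The one downside is that the other scales can no longer carry the primary claim.

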### Other outcome measures

#### Body composition

Height and weight will be measured. Body mass index, fat mass, lean body mass, abdominal adipose tissue and bone mineral density will also be assessed by conducting Dual-energy X-ray absorptiometry (DXA, Discovery densitometer from HOLOGIC, QDR 4500 W) using protocols reported in previous studies [43, 44]. This assessment tool has previously been used in breast cancer patients [45, 46].

### Muscular strength

The handgrip strength test will be assessed using a digital dynamometer (TKK 5101 Grip-D; Takey, Tokyo, Japan). Following the protocol described by Ruiz-Ruiz et al. [47], the optimal grip span will be determined by a simple algorithm to adapt the dynamometer. Throughout the whole test, BCS will be in a bipedal position; they have to put their arm in complete extension without touching any part of their body [18], repeating the test three times with each hand, alternately. There will be a delay of one minute between each test. The mean of the three tests will be used for the main analysis. This measurement has been demonstrated to be valid and reliable [48].

